### Secondary Outcome Measures

We will administer a sociodemographic and health questionnaire at baseline only, requesting the following personal information from participants: gender, age, ethnicity, marital status, highest level of education, employment and occupation, and some details about their cancer diagnosis and any other medical conditions.

Participants will complete a set of validated questionnaires preprogram and postprogram, to give an indication of changes in depression, anxiety, mental well-being, and confidence to self-manage their cancer across the intervention and control groups. These questionnaires are detailed below.

The Patient Health Questionnaire (PHQ-9) [35] is a 9-item measure that assesses the frequency of depression symptoms (eg, “over the past two weeks, how often have you been bothered by any of the following problems … i) little interest or pleasure in doing things; ii) feeling down, depressed or hopeless; iii) poor appetite or overeating”). Responses to each of the 9 items range from 0 to 3 (0=not at all, 1=several days, 2=more than half the days, 3=nearly every day), leading to a summed score between 0-27, with higher scores indicating greater severity of depression. Scores of ≥10 are presumed to be above the clinical range, and so scores of ≥10 are classed as “cases” of depression. Recovery rates are calculated as those patients who score ≥10 (cases) prior to treatment and <10 posttreatment.

The Generalized Anxiety Disorder scale (GAD-7) [36] is a 7-item scale measuring symptoms of generalized anxiety disorder (eg, “Over the past two weeks, how often have you been bothered by the following problems … i) feeling nervous, anxious or on edge; ii) trouble relaxing; iii) becoming easily annoyed or irritable”). Responses to all 7 items range from 0 to 3 (0=not at all, 1=several days, 2=more than half the days, 3=nearly every day), providing a total score of 0-21, with higher scores indicating greater anxiety. Scores of ≥8 are classed as “cases” of generalized anxiety disorder. Recovery rates are calculated as those patients who score ≥8 (cases) prior to treatment and <8 posttreatment.

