After providing informed consent to take part in the study, all participants will be guided through the process of completing the baseline questionnaires (Time 0; hereafter, T0). Upon completion of T0 questionnaires, participants will be randomized via the Qualtrics randomization function, to either attend the Hope Programme starting in May 2020 (intervention group [IG]) or in June 2020 (wait-list control group [WLCG]). Participants are notified which group they have been randomized to at the end of the survey. There will be approximately 30 participants in each group. The IG will then be sent an email link that provides access to the Hope Programme. Those randomized to the WLCG will be informed that they will receive an email link shortly before the start of the Hope Programme in June (ie, approximately 6 weeks later). After 6 weeks (T1), all participants will be emailed a link to the Qualtrics survey containing the secondary outcome questionnaires, and IG participants will also receive a participant debrief at T1. The debrief contains information reminding the participant why the study is being conducted and what will happen to the results, thanking them for their time, and includes sources of additional support if they experienced any distress through completing the questionnaires, such as their own general practitioner or the Samaritans. The WLCG also receive the survey link via email again, with secondary outcome measures and debrief, after they have received the intervention (T2). Table 1 provides a list of all digital study documents presented to participants at each time point (T0, T1, T2). All information and questionnaires at T0, T1, and T2 will be delivered via the Qualtrics survey platform. The Hope Programme will be delivered via the H4C platform.

**Table 1 table1:** Information and questionnaires presented to IG and WLCG participants at each time point (T0, T1, and T2), across the duration of the study.^a^

Study documents	T0	T1		T2
	IG and WLCG	IG	WLCG	WLCG
Participant information sheet	✓			
Informed consent	✓			
Sociodemographic and health questionnaire	✓			
Warwick Edinburgh Mental Wellbeing Scale	✓	✓	✓	✓
Patient Health Questionnaire	✓	✓	✓	✓
Generalized Anxiety Disorder scale	✓	✓	✓	✓
Patient Activation Measure	✓	✓	✓	✓
Poststudy debrief information		✓		✓

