### Monitoring

#### Data Monitoring

In this small feasibility trial, it was not deemed necessary to employ an independent data monitoring committee. However, participant data was screened at T0, T1, and T2 by the research team to check for indications of suicidal thoughts on the PHQ-9 questionnaire.

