#### Harms

Participants who indicate they are feeling suicidal at any point during the study on the PHQ-9 measure will be provided with the contact details of local mental health agencies and Samaritans, and will be encouraged to visit their general practitioner. We will also contact the MCS administrator. At postprogram, all participants’ data will be analyzed to examine if any people have reached a probable clinical level of depression or anxiety where they previously were not at this level. This will be recorded and listed as possible adverse effects of the intervention. These participants will be contacted and encouraged to visit their general practitioner and will be signposted to further sources of support as listed above.

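### The only stated rule for listing possible adverse effects is new depression or anxiety caseness, so new or worsened suicidal thoughts can go unlisted although they are screened at every questionnaire

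*Protocol article*

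**What the plan says.** The Harms section of the protocol article describes two processes.

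- **Care.** "Participants who indicate they are feeling suicidal at any point during the study on the PHQ-9 measure will be provided with the contact details" of mental health services and the Samaritans, and are encouraged to see their general practitioner. The Macmillan Cancer Support (MCS) administrator is also contacted.
- **Listing.** At postprogram the data are used to "examine if any people have reached a probable clinical level of depression or anxiety where they previously were not at this level". The next sentence reads: "This will be recorded and listed as possible adverse effects of the intervention".

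The Data Monitoring section adds that "participant data was screened at T0, T1, and T2 by the research team to check for indications of suicidal thoughts on the PHQ-9 questionnaire". According to Participant Timeline and Table 1, both arms answer the PHQ-9 at T0 and T1, and the wait-list group answers it again at T2, after its own programme.

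Secondary Outcome Measures gives the cutoffs. For the PHQ-9: "Scores of ≥10 are presumed to be above the clinical range, and so scores of ≥10 are classed as “cases” of depression". For the GAD-7: "Scores of ≥8 are classed as “cases” of generalized anxiety disorder".

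**The concern.** In the listing sentence, the word 'This' points back to new caseness and not to suicidal thoughts, which were dealt with earlier in the same paragraph. The sign that the team actively looks for at each questionnaire therefore has no stated path into the list of possible adverse effects. Caseness is a threshold on a total score and is a poor stand-in for change on one item. It misses people who stay well below the threshold and people who were already above it.

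What is at stake is the harm report. The article plans no independent data monitoring committee and no audit, so this list is the only harm-reporting output it describes. If it is compiled as written, the team planning the definitive trial would have no stated count of new or worsened suicidal thoughts.

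**Working it through.** The plan has no figure to reproduce here. The check is a reading of the rule, followed by score arithmetic.

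**1. Is there another listing rule?** None of the other sections of the article gives a rule for recording or listing adverse effects. Data Monitoring covers screening only. Statistical Methods promises descriptive summaries at baseline and postprogram, but does not mention harms.

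**2. Inputs.** Depression case: PHQ-9 total ≥10 (range 0–27). Anxiety case: GAD-7 total ≥8 (range 0–21). PHQ-9 scoring: "Responses to each of the 9 items range from 0 to 3". Assumption: exactly one PHQ-9 item asks about suicidal thoughts and is scored like the rest. The article quotes some items as examples, but not this one.

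**3. Who can be listed, by T0 status (T0 as reference).** A person is listed only on crossing a cutoff that they were previously below.

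| Case at T0 on | Depression route | Anxiety route |
|---|---|---|
| neither scale | open | open |
| depression only | closed | open |
| anxiety only | open | closed |
| both | closed | closed |

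This table needs no assumption about the item. For the intervention group, T0 is the only earlier assessment, so a participant who is a case on both scales has no route. For the wait-list group, postprogram is T2, and the rule does not say whether the earlier level is that at T0 or at T1. If it is T1, a participant who is a case on both scales at T0, falls below a cutoff by T1 and is a case again at T2 could be listed.

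**4. Does a change on the suicidality item trigger the depression route by itself?** Let s be the sum of the other 8 items (0 to 8 × 3 = 24), held fixed, and let the item go from a to b. Then T0 = s + a and T1 = s + b, and the person is newly listed only if s + a < 10 ≤ s + b.

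| Item change | T0 totals possible | T0 totals that give a new depression listing |
|---|---|---|
| 0 to 1 | 0–24 | 9 |
| 0 to 2 | 0–24 | 8, 9 |
| 0 to 3 | 0–24 | 7, 8, 9 |
| 1 to 2 | 1–25 | 9 |
| 1 to 3 | 1–25 | 8, 9 |
| 2 to 3 | 2–26 | 9 |

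For a rise from 0, that is 1, 2 or 3 of 25 possible totals. These are possible scores, not people, and they say nothing about frequency. In practice other items may move too, and the anxiety route may open separately. The table shows only that the depression cutoff does not by itself register a change in suicidal thoughts.

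**5. Two concrete cases.** A participant who moves from 0 to 3 on the item and scores 0 on the other eight has a total of 3, below 10, and is not a new depression case. A participant with a T0 total of 12 and 0 on the item, whose item rises to 3 with the rest unchanged, has a total of 12 + 3 = 15. They were already a case, so they are not new. Neither is listed unless they also become a new GAD-7 case.

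**The case against.** The strongest reply is that this is silence in a condensed article. The Harms section states one positive rule and does not say that nothing else will be listed, and a full protocol may hold the complete adverse-event procedure. This stands in part: a reader might infer that the plan excludes suicidal thoughts from the harm list, and the article does not say so. It does not dispose of the point, because the article is not silent on harms. It fixes an operational listing rule and, in the same paragraph, sends suicidal thoughts down a different route that ends in participant care.

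A second reply is that every positive answer has to be identified in order to act on it, and that survey data are linked by participant ID across T0, T1 and T2 (Confidentiality). Person-level change can therefore be derived. That is correct, but nothing stated requires it to be derived or listed.

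Two further inferences are tempting and should be resisted.

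- A reader might conclude that anyone who is a case on both scales at T0 can never be listed. The rule refers only to an earlier level and does not name T0, so this holds for the intervention group but not necessarily for the wait-list group at T2.
- A reader might conclude that participants are left unprotected. They are not: the care actions apply to every positive answer, whatever the total score.

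Finally, the exact definition of a worsening is partly a matter of judgement, and other definitions could be defended. That bears on the wording of the fix, not on whether the gap exists.

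**Conclusion.** The point holds as a minor harms-reporting improvement. Followed as written, the listing rule can omit new or worsened suicidal thoughts in participants who stay below both cutoffs, and in those who were already a case and do not newly cross the other cutoff. In the intervention group, being a case on both scales at T0 closes every route.

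The size cannot be put as a number of people, because the article gives no rate of suicidal thoughts and no baseline caseness for this sample. The primary feasibility outcomes do not depend on it. The progression criteria use recruitment, questionnaire completion and programme completion, not harms.

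The conclusion rests on reading 'This' as referring to the sentence just before it, and on no fuller listing rule existing elsewhere. The score arithmetic also assumes a single suicidality item scored 0–3. The closed routes for baseline cases do not depend on that assumption.

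**What to change.** Add one sentence to Harms, for example: *New suicidal thoughts (PHQ-9 suicidality item 0 at the previous assessment and 1 or more at the current one), and any increase on that item from a non-zero answer at the previous assessment, will also be recorded and listed as possible adverse effects.*

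Report number and percent by randomised arm at T1, among those who answered the item at both T0 and T1. Keep this descriptive, in line with the decision in Statistical Methods not to make between-group inferential comparisons. Report the wait-list change from T1 to T2 separately, since it follows that group's own programme. Leave the caseness rule and the care actions as they are.

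The cost is one sentence and one small table from an item already collected and screened, using IDs already linked. No new data are needed, so the change is still possible although data collection ended in August 2020. If it counts as a protocol amendment, it goes to the university ethics committee under the article's own amendment rule. The downside is that the counts will be small and cannot establish causation, and the harm report may look less favourable.

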#### Auditing

Auditing of trial conduct will not be necessary. The Hope Programme has been developed and tested in various studies, so the current feasibility trial will focus on recruitment and randomization procedures.

### Ethics and Dissemination

#### Research Ethics Approval

This study was reviewed and approved by the Coventry University Ethics Committee (P106024).

#### Protocol Amendments

Any amendments to the protocol will be submitted to the Coventry University Ethics Committee for review, and any research study activity will be suspended until approval is granted.

#### Consent

Informed consent will be taken online via Qualtrics. Participants will be required to answer “yes” to all consent statements before proceeding to the study questionnaires. If participants answer “no” to any consent statements, they will be directed to the end of the survey and no data will be collected. Consent statements for this study are included in Multimedia Appendix 2.

#### Confidentiality

MCS will send names and email addresses of interested participants to H4C (with the assent of participants), who will email interested participants introductory information and a link to the study website (Qualtrics). At the point of consent, participants will be assigned a unique identifier (ID) through Qualtrics, which will be used to link study data from multiple timepoints (T0, T1, T2). Participant data will be identifiable via this unique ID for the duration of the study. For the prize draw, this unique ID will be linked back to the participant name and email address only for email delivery of the prize (£50 Amazon voucher).

#### Access to Data

[name] will have access to the final data set.

#### Ancillary and Posttrial Care

There is no postprogram follow-up scheduled after the T1 questionnaires for IG, and the T2 questionnaires for WLCG. However, a participant debrief is provided at the end of the study, giving details of where participants can find additional support if they feel they need it.

#### Dissemination Policy

The results of the feasibility RCT will be submitted for publication via the open access route in a relevant journal (eg, Journal of Medical Internet Research), and a lay summary of the findings will be presented in a blog on the H4C website for participants to access. A link to this blog will be emailed to all participants by H4C.

## Results

Recruitment into this feasibility RCT began in April 2020, with all participants completing informed consent and baseline questionnaires before being randomized. Data collection from postprogram questionnaires was completed at the end of August 2020.

## Discussion

### Study Rationale

This feasibility trial is designed to provide evidence about whether it is possible to conduct a definitive trial of a digital self-management program for people with cancer. Digital health care has become more important than ever in the wake of COVID-19, and provision of an acceptable and effective digital self-management program for people with cancer is both timely and necessary [2,19,20].

### Strengths and Limitations

Digital delivery of the Hope Programme has rapidly become essential in light of the COVID-19 pandemic, and the resulting social distancing measures required for those who are clinically vulnerable or required to quarantine. Owing to recent research revealing the number of people with cancer who have experienced declining mental health and increasing fear during the pandemic [3], the Hope Programme is well placed to deliver timely and much-needed support for people with cancer, particularly while treatments and contact with health care teams are reduced [2].

It is noteworthy that there is not always a linear relationship between time spent in a digital intervention, the number of sessions completed, and participant outcomes [44]. For example, it is possible that the participants who access only a couple of sessions may be “e-attainers” (as described in [45]). These participants may achieve what they need from the program, such as practicing gratitude, or gaining reassurance that their challenges are shared by others [46]. In our comprehensive statistical analyses, we plan to use a combination of data from our usability measures and the user engagement data extracted from the platform to develop a more thorough understanding of engagement and attrition, which can then be used to inform the content and design of future versions of the Hope Programme.

A challenge for many digital interventions is completion of postprogram questionnaires. Achieving an acceptable postprogram questionnaire completion rate is a key criterion for progression to a definitive trial. In this feasibility trial, we have included entry to a prize draw for those that complete the postprogram questionnaires. This will enable us to determine whether this is sufficient to secure an acceptable postprogram completion rate in this population. Exploring the feasibility of achieving acceptable completion rates for questionnaires is particularly pertinent with a wait-list control group design. There is some evidence that wait-list controls for studies of psychological interventions may overestimate intervention effects relative to other forms of control group [47]. Wait-list control participants are hypothesized to delay taking action while they are waiting relative to no active treatment control participants [48]. Testing the feasibility of this approach will enable us to establish whether this is an acceptable trial design and an ethical approach to RCTs for people with cancer in these unprecedented times.

## Appendix

Multimedia Appendix 1 Hope Programme development and content.

Multimedia Appendix 2 Informed consent materials.

## Abbreviations

CONSORT: Consolidated Standards of Reporting Trials
GAD-7: Generalized Anxiety Disorder scale
H4C: Hope for The Community
MCS: Macmillan Cancer Support
NHS: National Health Service
PAM: Patient Activation Measure
PHQ-9: Patient Health Questionnaire
PIS: participant information sheet
SPIRIT: Standard Protocol Items: Recommendations for Interventional Trials
WEMWBS: Warwick Edinburgh Mental Wellbeing Scale
